### Sample size

We calculated the minimum number of FGR participants using PASS (NC, USA). Based on a published study, we set an α-error of 0.05 and a β-error of 80%, and the minimum number of FGR participants required was 472. Considering a follow-up loss rate of 10%, we need to enroll at least 519 pregnant women with FGR fetuses. Therefore, the minimum number of total participants that we anticipate including is 1,050 (525 FGR participants and 525 control participants). The researchers will first review the medical records and include eligible participants retrospectively.

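### The sample-size paragraph states a β-error of 80%, which means 20% power, and gives two FGR minimums, 519 and 525, of which only 525 survives the stated 10% loss

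*Protocol article*

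**What the plan says.** All the figures are in one paragraph, the Sample size section of the protocol article.

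- Error rates and base number: "we set an α-error of 0.05 and a β-error of 80%, and the minimum number of FGR participants required was 472". The only source given for the effect is "Based on a published study". No effect size, event rate, standard deviation, test or sidedness follows.
- Loss allowance: "Considering a follow-up loss rate of 10%, we need to enroll at least 519 pregnant women with FGR fetuses".
- Planned total, in the next sentence and presented as following from the one before: "1,050 (525 FGR participants and 525 control participants".

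The Outcomes section places the primary outcome within the FGR group, so the FGR number is the one that matters for the main question.

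**The concern.** Two things in the paragraph are wrong as written.

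First, β is the type II error rate and power is 1 − β. A β-error of 80% therefore declares 20% power. This is the only statement about power in the article, so a reader has no other sentence to set it against.

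Second, the paragraph gives one floor for the FGR group and then a different one. To keep n participants after losing a fraction d, n must be divided by (1 − d). Multiplying by (1 + d) falls slightly short. The figure 519 comes from multiplying. The figure 525 agrees with dividing. The second is introduced as a consequence of the first, yet twice 519 is 1,038, not 1,050.

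At stake is whether a reader can rely on the stated error rate and on a single required number of FGR participants.

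**Working it through.** **Inputs, all from the Sample size section**

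- α = 0.05, sidedness not stated
- β stated as 80%
- minimum FGR number before loss, n = 472
- loss fraction, d = 10%
- FGR number after loss, stated first as 519 and then as 525
- planned total 1,050

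**Step 1: the power statement**

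Power = 1 − β = 1 − 0.80 = 0.20. With the usual convention of β = 0.20, power would be 0.80. Deciding between the two from the number 472 would need the effect size and the test, and neither is given. So 472 cannot be reproduced under either reading.

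**Step 2: reproduce 519**

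n × (1 + d) = 472 × 1.10 = 519.2, which gives 519 when rounded down.

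**Step 3: the number that keeps 472 after a 10% loss**

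n / (1 − d) = 472 / 0.90 = 524.4, rounded up to 525. This equals the FGR number in the next sentence, and 2 × 525 = 1,050 matches the planned total.

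**Step 4: what remains after the stated loss**

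| FGR enrolled | × 0.90 | Against 472 |
|---|---|---|
| 519 | 467.1 | below |
| 524 | 471.6 | below |
| 525 | 472.5 | meets it |

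525 is the smallest whole number that meets the requirement. The gap between the two minimums is 525 − 519 = 6, and 6/525 = 1.1%.

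**Step 5: the cost in power if only 519 were enrolled**

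Assume that 472 gives 80% power, two-sided α = 0.05, with a normal approximation. The standardised effect at n = 472 is then 1.960 + 0.842 = 2.802, and it scales with the square root of n.

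- With 467.1 analysed: 2.802 × √(467.1/472) − 1.960 ≈ 0.827, so power is 79.6%.
- With 472.5 analysed: power is 80.0%.

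The loss is about 0.4 percentage points.

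**The case against.** The best defence is that nothing in the planned study falls short. The sentence straight after 519 sets the FGR number at 525, and 525 less 10% is 472.5. A plan for 525 also satisfies a floor of 519, so the two figures do not strictly contradict each other. On this view 519 is an intermediate number from a cruder formula, overtaken by the next sentence. The defence also holds that the β wording is an obvious slip that changes no number.

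Most of this stands. There is no shortfall in planned enrolment, and the 519 error is negligible in effect. Two points survive it. The β statement is wrong on any reading, and the article offers nothing to settle what was entered in the software. The paragraph also still contains two minimums, and the smaller one fails the paragraph's own requirement.

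A reader might be tempted to go further in three ways, none of which the document supports.

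- **That the study really has 20% power.** If 472 had been computed at β = 0.80, reaching 80% power for the same effect would take ((1.960 + 0.842)/(1.960 − 0.842))² ≈ 6.3 times as many FGR participants, about 2,960 (two-sided 0.05 assumed). Nothing in the article suggests that the software was run this way, and without the effect size this case cannot be tested.
- **That record extraction might stop at 519.** No stopping rule at that number is stated. The paragraph plans 525 per group, and the text under Exclusion criteria defines the records by a delivery window, March 2016 to March 2023.
- **That calling the 10% a follow-up loss is an error of substance in a retrospective study.** The label fits awkwardly. But the article does not say whether the exclusions for missing data apply before or after the 525 are counted, and renaming the allowance changes no figure.

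**Conclusion.** The point holds in a limited form. The stated β-error of 80% is wrong as written if the usual 80% power was intended. That intention is very likely, but it cannot be confirmed from the article. Of the two FGR minimums, 519 misses 472 by about 5 participants after the stated loss, and 525 meets it. Since 525 is what the study plans, planned enrolment is sufficient for the stated requirement of 472. Whether 472 is itself right cannot be judged here.

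The size is small: 1.1% between the two minimums, and about 0.4 percentage points of power if only 519 were enrolled. The power figure assumes that 472 corresponds to 80% power at two-sided 0.05, under a normal approximation.

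Severity is minor to moderate. It is more than clerical, because a stated error rate and a required sample size are figures that readers rely on. It is not serious, because the likely correction leaves the plan unchanged.

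**What to change.** 1. Check the input to the sample-size software. If power was 0.80, state a β-error of 20% (power 80%). If the input was different, restate the achieved power.
2. Replace 519 with 525, derived as 472/0.90 = 524.4 rounded up, so that the paragraph has one FGR minimum and the total of 1,050 follows from it.

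The cost is one look at the saved software settings and two changes of wording. The enrolment target of 525 per group does not change.

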### Outcomes

The primary outcome is the association of UV absolute flow, placental thickness, and uterine wall thickness with adverse perinatal outcomes in the FGR group to differentiate genuinely growth-restricted fetuses from those who are constitutionally small. The secondary outcome is to evaluate the differences in U-AID indices (UtA, UA, MCA, and UV flow, placental and uterine wall thickness, and estimated fetal body weight) between the FGR and control group will be evaluated.

### Ultrasonographic uteroplacental-fetal biometrics and Doppler (U-AID) indices

We will collect the ultrasonographic uteroplacental-fetal biometric measurements and U-AID indices listed in Table 1 in each trimester of pregnancy. During the first trimester of pregnancy, we will collect ultrasonographic measurements from 11^0/7^ to 13^6/7^ weeks of gestation. The measurements will be assessed from 18^0/7^ to 23^6/7^ weeks of gestation during the second trimester of pregnancy and from 30^0/7^ to 36^6/7^ weeks of gestation during the third trimester of pregnancy. The ultrasound model used and the clinical experience years of clinicians who measure U-AID indices will also be documented. To assess fetal growth, crown to rump length, biparietal diameter, head circumference, abdominal circumference, femur length, and estimated body weight will be evaluated. UA Doppler which was measured in a free cord loop and MCA Doppler which was measured in the proximal third of the MCA will be selected. The systolic/diastolic ratio (S/D ratio), pulsatile index (PI), and resistive index (RI) in the UtA, UA, MCA, and UV will be calculated as reported previously [22, 23]. The Doppler indices will be calculated as follows.

S/D ratio = peak systolic velocity [cm/sec] (S)–end-diastolic velocity [cm/sec] (D)PI = S–D / mean of S and D (M)RI = S–D / SNotch index = early diastolic flow velocity [cm/sec]/ peak diastolic flow velocity [cm/sec]UV absolute flow [ml/min] = UV cross-sectional area [cm^2^] * UV mean velocity [cm/sec] * 60

**Table 1 pone.0298060.t001:** Ultrasonographic uteroplacental-fetal biometric measurements and Doppler indices of the U-AID cohort.

**Uteroplacental-fetal biometry**	**Timing of measurement**	**Unit**
Crown to rump length	First trimester	Mm
Biparietal diameter	Second trimester, Third trimester	cm
Head circumference	Second trimester, Third trimester	cm
Abdominal circumference	Second trimester, Third trimester	cm
Femur length	Second trimester, Third trimester	cm
Estimated fetal weight	Second trimester, Third trimester	g
Placental thickness	Second trimester, Third trimester	mm
Uterine wall thickness	First trimester, Second trimester, Third trimester	mm
**Uteroplacental-fetal Doppler**		**Indices**
Uterine artery	First trimester, Second trimester, Third trimester	S/D ratio, PI, RI, early diastolic notch index
Umbilical artery	Second trimester, Third trimester	S/D ratio, PI, RI
Middle cerebral artery	Second trimester, Third trimester	S/D ratio, PI, RI
Ductus venosus	Second trimester, Third trimester	S/D ratio, PI, RI
Umbilical vein	Second trimester, Third trimester	Pulsation, cross-sectional diameter, mean velocity, absolute flow

Abbreviation: PI, pulsatile index; RI, resistive index; S/D ratio, systolic/diastolic ratio

The placental thickness and the uterine wall thickness which were measured through the sagittal section at the location of cord insertion will be collected. (Fig 1). The uterine wall was considered as a homogenous layer above the placenta.

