### Statistical methods

The distribution of U-AID indices according to AC, BPD, EFW and gestational age will be assessed. The study population will be divided into two groups, the FGR group which includes participants with FGR fetuses, and the control group includes participants with normal growth fetus. First of all, we will compare the differences in U-AID indices according to adverse perinatal outcomes with in FGR group. Secondly, the difference of U-AID indices between the two groups will be compared. Continuous variables will be presented as the mean ± standard deviation or median [interquartile range] and compared by the Mann-Whitney U test or independent t-test according to the distribution of each variable. Categorical variables will be presented as the number of observations (percent) and compared by the chi-squared test or Fisher’s exact test. To determine the contribution of all the collected variables and Doppler findings to adverse perinatal outcomes of the FGR fetuses, multivariable logistic regression analysis with backward stepwise elimination will be used.

All statistical analyses will be performed using IBM SPSS statistics version 23.0 (SPSS Inc., Chicago, IL, USA) and R version 4.2.1 (http://www.r-project.org).

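### The printed S/D formula is a difference, the printed PI is a fixed function of RI, and the text and Table 1 disagree on whether the umbilical vein or the ductus venosus gets these indices

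*Protocol article*

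**What the plan says.** All the definitions are in the protocol article, Methods, in the section on U-AID indices. A lead-in sentence presents the list of formulas as the way the indices are to be computed.

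- S/D ratio: "S/D ratio = peak systolic velocity [cm/sec] (S)–end-diastolic velocity [cm/sec] (D"). The abbreviation note under Table 1 expands the same index as "S/D ratio, systolic/diastolic ratio".
- PI: "PI = S–D / mean of S and D (M").
- RI: the difference between S and D, over S.
- Vessels, in the text: the S/D ratio, PI and "resistive index (RI) in the UtA, UA, MCA, and UV will be calculated as reported previously".
- Vessels, in Table 1: S/D ratio, PI and RI are listed for the uterine artery (with a notch index), the umbilical artery, the middle cerebral artery and the ductus venosus (DV). The umbilical vein (UV) row lists only "Pulsation, cross-sectional diameter, mean velocity, absolute flow".

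Under Statistical methods, U-AID indices are compared by adverse outcome within the FGR group, then between the FGR and control groups, by t-test or Mann-Whitney test. For the contribution of all collected variables and Doppler findings to adverse outcome in the FGR fetuses, "multivariable logistic regression analysis with backward stepwise elimination will be used".

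**The concern.** These are stated calculation rules, and three things in them do not hold together.

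First, a ratio of two velocities has no unit and does not change if both velocities are scaled together. A difference of two velocities does. An S/D variable coded as printed would measure partly how fast the blood moves and not only the shape of the waveform.

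Second, if the denominator of PI is built from S and D alone, PI uses the same two numbers as RI. It then cannot carry anything that RI does not.

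Third, an analyst following the text would derive a different set of variables from one following Table 1.

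What is at stake is the secondary comparison of indices between groups and the Doppler candidates entering the multivariable model.

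**Working it through.** The document states no figure to reproduce, so the check is algebra on the printed formulas, followed by examples. The document gives no velocities. **Every S, D and RI value below is an assumption for illustration.**

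**1. S/D as printed.** The same list uses the slash for division (PI, RI, notch index) and the dash for subtraction (PI, RI), so the dash in the S/D line reads as a minus sign.

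| S, D (cm/sec) | S ÷ D | S − D (printed) |
|---|---|---|
| 60, 20 | 3.0 | 40 |
| 45, 15 | 3.0 | 30 |
| 30, 10 | 3.0 | 20 |

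Three waveforms with one ratio get three values, a two-fold spread due to velocity alone. In a simulation with S around 45 (SD 10) cm/sec and RI around 0.65 (SD 0.07), the rank correlation between S − D and S ÷ D was 0.42.

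**2. PI as printed.** Read the numerator as (S − D) and put M = (S + D)/2:

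- PI = (S − D)/[(S + D)/2] = 2(S − D)/(S + D).
- RI = (S − D)/S, so D = S(1 − RI) and S + D = S(2 − RI).
- Hence PI = 2·RI/(2 − RI). Its slope in RI is 4/(2 − RI)², which is always positive.

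Checks: S = 60, D = 20 gives RI = 0.667 and PI = 40/40 = 1.000, and 2(0.667)/(1.333) = 1.000. S = 50, D = 10 gives RI = 0.800 and PI = 40/30 = 1.333, and 1.6/1.2 = 1.333.

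Because the function is strictly increasing, a Mann-Whitney test gives the same result on PI as on RI. With RI uniform over an assumed range, the Pearson correlation r and the variance inflation factor 1/(1 − r²) are:

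| RI range | r | VIF |
|---|---|---|
| 0.4 to 0.8 | 0.997 | about 182 |
| 0.5 to 0.9 | 0.997 | about 156 |
| 0.3 to 0.95 | 0.992 | about 65 |

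**3. How far the printed PI may lie from a cycle-mean PI.** Assume the mean velocity over the cycle is M = D + f(S − D). The printed formula is the special case f = 0.5.

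| S, D | f = 1/3 | f = 0.45 | Printed |
|---|---|---|---|
| 60, 20 | 40/33.3 = 1.20 | 40/38 = 1.05 | 1.00 |
| 50, 10 | 40/23.3 = 1.71 | 40/28 = 1.43 | 1.33 |
| 50, 0 | 50/16.7 = 3.00 | 50/22.5 = 2.22 | 2.00 |

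The gap widens as end-diastolic velocity falls, and the printed PI cannot exceed 2 while D is at least 0.

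**4. Vessels.** The text lists UtA, UA, MCA and UV. Table 1 gives S/D, PI and RI to UtA, UA, MCA and DV. Three vessels agree; the fourth differs.

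**The case against.** The strongest reply is that these are slips of reporting. The study is retrospective and the indices are extracted from medical records. The text refers to previously reported methods, and the name of the S/D index makes the intended quotient plain. On that view no wrong value need ever be produced. This is possible, but the article does not say that recorded values are used unchanged, and it presents the formulas as the method of calculation. They should be right.

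A second reply is that redundancy with RI does not show an index to be wrong. This largely stands. A correct S/D equals 1/(1 − RI), also an exact function of RI, so redundancy among the indices survives the correction. A cycle-mean PI would still track RI closely: in the simulation with f around 0.45 (SD 0.06), its rank correlation with RI was 0.97 to 0.99. What the printed denominator does is turn a strong correlation into an identity. The cycle-mean definition is not in the article either, and the cited method papers were not available for this review.

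Several stronger readings are tempting but not supported:

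- *PI disagrees with the scanner in every case, or the 13 hospitals hold mixed definitions.* The article does not describe scanner-reported PI or say which values would be recomputed. Where the cycle mean happens to equal (S + D)/2, the two definitions agree.
- *Without brackets, PI means S − (D/M).* The list may have lost its layout in the text as read, and (S − D)/M is the obvious meaning.
- *The printed PI cannot grade the most abnormal waveforms.* It is constant only at D = 0, where RI is constant too (1.0). With reversed flow it varies again.
- *DV indices are left out of the plan.* The section commits to collecting what Table 1 lists, and Table 1 includes them. The defect is a mismatch. It is not certain which side erred: the U-AID list under Outcomes also names UV flow and not DV.
- *The primary analysis rests on wrong formulas.* The named exposures are UV absolute flow, placental thickness and uterine wall thickness, and none is computed from S/D, PI or RI.

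**Conclusion.** The point holds within limits. The S/D formula is wrong as written and contradicts the name of the index; that conclusion rests on no assumption. The identity PI = 2·RI/(2 − RI) is exact given the printed denominator. The vessel lists in the text and Table 1 cannot both be followed.

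The sizes are illustrative. They are a two-fold spread in S/D at a fixed ratio of 3.0, a VIF for PI with RI of about 65 to 182, and a printed PI below a cycle-mean PI by 0.05 to 1.00 in the cases shown. All depend on assumed velocities, RI ranges and waveform shape.

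The effect falls on the secondary FGR-versus-control comparison and on the Doppler variables in the multivariable model. The values of the three primary exposures are unaffected; they could be touched only indirectly, through Doppler covariates in that model. Whether any wrong value has been computed cannot be told from the article.

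**What to change.** - Print the S/D ratio as S ÷ D.
- Print PI as (S − D) divided by the mean velocity over the cardiac cycle, after checking this against the methods the article cites. Bracket the numerators of PI and RI for clarity.
- Where only S and D are available for recalculation, take the PI recorded in the notes and do not rebuild it from those two values. State in the protocol which PI values are recorded and which are recomputed.
- Reconcile the vessel list in the text with Table 1, so that one list says which vessels get S/D, PI and RI and what is derived for UV and DV.
- Check any derived variables already coded from the printed formulas and recompute them where needed.

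The cost is a few words of text and one check of the derivation code. No new data are needed, and neither the design nor the sample size changes.

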**Fig 1 pone.0298060.g001:**
[figure not shown]
The measurement of placental and uterine wall thickness.

### Adverse perinatal outcomes

Pregnancy and perinatal outcomes will be acquired from medical charts. The adverse perinatal outcomes of the current study are listed in Table 2. The composite morbidity of neonates is defined as one of the following: sepsis, respiratory distress syndrome, necrotizing enterocolitis, or intraventricular hemorrhage before discharge.

**Table 2 pone.0298060.t002:** Adverse perinatal outcomes in the U-AID cohort.

**Pregnancy outcomes**
Preeclampsia
Emergency cesarean section due to non-reassuring fetal heartbeat
Intrauterine fetal demise
**Neonatal outcomes**
Birthweight
Admission to neonatal intensive care unit (NICU),
Sepsis before discharge
Respiratory distress syndrome before discharge
Necrotizing enterocolitis before discharge
Intraventricular hemorrhage before discharge
Periventricular leukomalacia
Neonatal death before discharge

### Data management

The study will be managed according to General Data Protection Regulations and Good Clinical Practice (GCP). Data will be collected securely on case report forms (CRFs) and each participant will be assigned a unique number for pseudonymization. All study data will be stored securely on password-protected PCs and only accessible to the researchers of the current study. Paper CRFs, paper consent forms, and any paper records of study data will be kept in locked drawers or cabinets in a secure location.

### Statistical methods

The distribution of U-AID indices according to AC, BPD, EFW and gestational age will be assessed. The study population will be divided into two groups, the FGR group which includes participants with FGR fetuses, and the control group includes participants with normal growth fetus. First of all, we will compare the differences in U-AID indices according to adverse perinatal outcomes with in FGR group. Secondly, the difference of U-AID indices between the two groups will be compared. Continuous variables will be presented as the mean ± standard deviation or median [interquartile range] and compared by the Mann-Whitney U test or independent t-test according to the distribution of each variable. Categorical variables will be presented as the number of observations (percent) and compared by the chi-squared test or Fisher’s exact test. To determine the contribution of all the collected variables and Doppler findings to adverse perinatal outcomes of the FGR fetuses, multivariable logistic regression analysis with backward stepwise elimination will be used.

All statistical analyses will be performed using IBM SPSS statistics version 23.0 (SPSS Inc., Chicago, IL, USA) and R version 4.2.1 (http://www.r-project.org).

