Even though the definition of FGR may defer between guidelines, consistently worse perinatal outcomes of FGR fetuses with abnormal UA Doppler results have been reported compared to those with normal UA Doppler results [6–9]. Therefore, fetal vascular Doppler examinations, including UA Doppler, are important in distinguishing a pathologically growth-restricted fetus from a small but healthy fetus. Several studies predicted the perinatal outcomes of fetuses with growth restriction and these studies mainly focused on the Doppler examination of specific vessels, such as the UA, MCA, or ductus venosus (DV) [6–12]. However, besides the UA, MCA, or DV, uteroplacental-fetal circulation also consists of other components affecting fetal growth. For example, umbilical vein (UV) flow and placental thickness, which are components of uteroplacental-fetal circulation, have already been shown to be associated with fetal growth. Ferrazzi et al. reported that UV flow per unit head circumference (HC) was decreased in FGR fetuses [13]. Another study reported that venous flow was also reduced in FGR fetuses [14]. In a previous study assessing the correlation between placental thickness and small for gestational age (SGA) neonates, the placental thickness-to-EFW ratio was higher in SGA neonates compared to non-SGA neonates [15]. In addition, a thick placenta was reported to be associated with adverse perinatal outcomes [16]. In this research, we aim to focus on the uterine wall, in conjunction with the umbilical vein. The uterine wall is a distinctive aspect of this study, as it has been neglected in previous research on FGR. The causes of a thick uterine wall observed in ultrasonography are typically categorized into three main factors: sustained uterine wall contractions, adenomyosis, and uterine fibroids [17, 18]. If a thick uterine wall is observed in a pregnant woman without a history of uterine fibroids or adenomyosis, it may be attributed to a sustained uterine contraction. The uterine contractions are known to lead to a decrease in uteroplacental blood flow [18–20]. Taking this into consideration, uterine wall thickness may be associated with the uteroplacental blood flow. The hypothesis that uterine wall thickness may impact fetal growth is one of the key starting points for our research.

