### Exclusion criteria

Pregnant women with missing value of UV flow, placental thickness, and uterine wall thicknessPregnant women with fetuses with possible structural anomalies or abnormal insertion of umbilical cord found on ultrasoundPregnant women with fetuses with chromosomal abnormalitiesPregnant women who are proven to have an intrauterine infectionPregnant women who have limited data on clinical characteristics related to pregnancy and perinatal outcome

In this study, we define FGR as a status where both of the following 2 conditions are met; (1) an EFW or AC below the 10th percentile for gestational age during the second or third trimester of pregnancy and (2) birthweight below the 10th percentile for gestational age [3]. The INTERGROWTH-21^st^ growth chart is used for biometry and birthweights [21]. The FGR group includes both early-onset FGR and late-onset FGR. The control group includes participants with a fetus whose EFW and AC are in the range of 10^th^ to 90^th^ percentile for gestational age. The control group will be selected through 1:1 matching based on age, parity, and presence or absence of preeclampsia. The clinical information and U-AID indices of pregnant women who delivered between March 2016 and March 2023 will be extracted from the medical records.

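### The group comparisons use raw, gestation-dependent indices over scan windows of 6 and 7 weeks, with no guaranteed adjustment for gestational age at scan

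*Protocol article*

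**What the plan says.** All references are to the protocol article.

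- **Exposures.** Outcomes names UV absolute flow, placental thickness and uterine wall thickness as the primary exposures. The U-AID indices section defines UV flow as area times mean velocity times 60, in ml/min. Table 1 gives both thicknesses in mm. No size scaling or gestational-age standardisation is stated.
- **Scan windows.** Second trimester: "The measurements will be assessed from 18^0/7^ to 23^6/7^ weeks of gestation during the second trimester of pregnancy". Third trimester: "from 30^0/7^ to 36^6/7^ weeks of gestation during the third trimester of pregnancy". First trimester: "we will collect ultrasonographic measurements from 11^0/7^ to 13^6/7^ weeks of gestation"; of the three exposures, Table 1 lists only uterine wall thickness there.
- **Comparisons.** Statistical methods begins with "First of all, we will compare the differences in U-AID indices according to adverse perinatal outcomes with in FGR group" and then compares FGR with control. Continuous variables are "compared by the Mann-Whitney U test or independent t-test according to the distribution of each variable".
- **Controls.** Under Exclusion criteria: "The control group will be selected through 1:1 matching based on age, parity, and presence or absence of preeclampsia".
- **Where gestational age or fetal size appears.** Statistical methods will look at how the indices are distributed by AC, BPD, EFW and gestational age. It also plans a backward-elimination logistic model for adverse outcomes in FGR fetuses, drawing on everything collected.
- **Precedent.** The Introduction supports the exposures partly with size-scaled results: "UV flow per unit head circumference (HC) was decreased in FGR fetuses", and a placental thickness-to-EFW ratio.
- **EFW as an index.** The secondary outcome lists it among the indices to be contrasted: "estimated fetal body weight) between the FGR and control group will be evaluated".

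**The concern.** Over six or seven weeks of pregnancy, an absolute flow in ml/min should rise as the fetus grows, and placental thickness may change too. A two-sample test on raw values cannot tell a low value for gestation from a value taken earlier in the window. If the adverse-outcome group was scanned earlier on average, its mean UV flow is lower even when flow for gestation is the same.

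A timing gap is plausible in two places, though the article documents neither:

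- **Within FGR, third trimester.** A fetus delivered during the 30+0 to 36+6 window can only have been scanned before delivery. Several listed neonatal outcomes (respiratory distress syndrome, intraventricular haemorrhage, NICU admission) plausibly go with early delivery.
- **FGR versus control.** The Discussion says that Doppler is not usually measured when EFW is normal. Controls with complete data may therefore have been scanned for other reasons and at other times than FGR cases.

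At stake is the stated aim of separating truly restricted from constitutionally small fetuses. A finding of low UV flow could partly mean that the scan was done earlier.

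**Working it through.** **1. The plan's own figures.** The 472 FGR participants cannot be recomputed, because no effect size, SD, event rate or test is given. The loss step can be followed: 472 × 1.10 = 519.2 (stated: 519), and 472 / 0.90 = 524.4, rounded up to 525 (the planned number per group; 2 × 525 = 1,050). The point here does not depend on these figures; 472 and 525 only set the precision used below.

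**2. Window widths, counting both end days.**
- 11+0 to 13+6: 21 days = 3.0 weeks
- 18+0 to 23+6: 42 days = 6.0 weeks
- 30+0 to 36+6: 49 days = 7.0 weeks

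**3. Where adjustment for scan timing could enter.**

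| Analysis | Gestational age at scan | Fetal size |
|---|---|---|
| Within-FGR t-test / Mann-Whitney | no | no |
| FGR-control t-test / Mann-Whitney | no; not a matching variable | no |
| Logistic model within FGR | not named; could be a candidate | EFW and AC are candidates; can be eliminated |

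**4. Size of the effect, with no true association.** Growth rate, spread, event rate and timing gap are all assumptions.

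*Illustration A: UV flow, 7-week window.* Assumed: growth g of 7-11% per week; between-fetus CV of 25-35% at a given gestation; 20% adverse outcomes, so 94.4 versus 377.6 of 472; scan dates spread uniformly over the window.

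- Standard error in SD units: √(1/94.4 + 1/377.6) = 0.115. Smallest difference detectable with 80% power: 2.80 × 0.115 = 0.32 SD.
- Shift from a 1-week gap: (e^g − 1)/CV. Low end (g = 0.07, CV = 0.35): 0.0725/0.35 = 0.207. High end (g = 0.11, CV = 0.25): 0.1163/0.25 = 0.465.
- The raw SD also contains the spread in scan dates. Their SD is 7/√12 = 2.02 weeks and the slope is g/CV = 0.20 or 0.44 SD per week, so the raw SD is √(1 + (0.20 × 2.02)²) = 1.079 or √(1 + (0.44 × 2.02)²) = 1.338.
- Standardised shift: 0.207/1.079 = 0.192, or 0.465/1.338 = 0.348. This is about 0.6 to 1.1 times the detectable difference.
- Rejection probability, Φ(d/SE − 1.96) + Φ(−d/SE − 1.96): d/SE is 1.67 or 3.02, giving **39% to 86%**. For a half-week gap it is 13% to 31%.
- FGR versus control, 525 per group, SE = √(2/525) = 0.0617: 88% to 100% at one week, 33% to 78% at half a week.

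*Illustration B: simulation.* 472 FGR pregnancies, 25% adverse outcomes, 7-week window, 2,000 runs per setting, slope 0.05-0.3 residual SD per week. Raw t-test rejection at nominal 5%:

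| Gap in mean scan timing | 0.05 | 0.1 | 0.2 | 0.3 |
|---|---|---|---|---|
| 0 weeks | 5% | 5% | 5% | 6% |
| 0.5 weeks | 5% | 7% | 14% | 23% |
| 1 week | 7% | 16% | 43% | 70% |
| 2 weeks | 16% | 44% | 95% | 100% |

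With gestational age at scan in the model, rejection is 4-6% in every setting.

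Taken together, a 1-week gap within FGR gives about 7% (flat index) to 86% (steep index with small spread). With no gap there is no inflation.

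**The case against.** **The plan does contain a multivariable model.** A reader might infer that nothing is adjusted for timing or size anywhere. The article does not support that. The logistic model addresses the primary association and draws on all collected variables. EFW, AC, HC, BPD and femur length are among these, and EFW in grams partly carries gestation. This stands as a correction to the strong reading. It does not settle the matter: gestational age at scan is not named, backward elimination can remove any term, and the FGR-control contrast is outside the model.

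**The article is condensed.** Covariate coding is commonly left to an analysis plan, and looking at the indices by gestational age could feed into the tests. However, the article does fix the scale, the windows, the matching variables and the tests. A t-test or Mann-Whitney test on the stated scale takes no covariate.

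**The false-positive rates are assumed.** This stands in full: no growth rate, spread, event rate or timing gap is in the article. A reader might also infer that false positives are nearly certain. Illustration A without the extra variance from scan dates would give 44-98% at one week, but a raw test over a 7-week window does face that variance.

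**The early-delivery mechanism is limited.** It applies mainly to deliveries inside the third-trimester window and hardly at all to 18+0 to 23+6. For uterine wall thickness a gestational trend is less clear. Both limits stand.

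**Absolute flow is a deliberate choice.** Size-scaled results in the Introduction do not make it an error, since fetal size may lie on the causal path and scaling changes the question. This stands.

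**EFW is not fully fixed by the group definition.** Membership may rest on AC, or on EFW in another trimester. So the EFW contrast is only partly circular, and a minor matter.

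**Conclusion.** The concern holds in a limited form. As written, both group comparisons test raw indices over windows of 6 and 7 weeks without adjustment, and no part of the plan guarantees that gestational age at scan is accounted for. Bias follows only if two conditions are met: the groups differ in mean scan timing, and the index changes with gestation. The second is expected for UV flow and less clear for uterine wall thickness. The first is plausible, chiefly in the third trimester and against controls, but undocumented.

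Its size cannot be taken from the article. The false-positive rate within FGR for a 1-week gap runs from about 7% to 86% under the assumed inputs, and is near 5% with no gap. The article does not support the stronger readings that the plan has no adjustment at all, that a spurious result is nearly certain, or that absolute UV flow is the wrong exposure. The change is still worth making before analysis, because it removes the problem under every setting simulated.

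**What to change.** 1. Express each gestation-dependent index as a gestational-age-specific z-score and run both group comparisons on that scale. Alternatively, replace the two-sample tests by regressions that include exact gestational age at scan (weeks and days), for example as a spline.
2. Force gestational age at scan into the logistic model and exempt it from backward elimination.
3. In the FGR-control contrast, match on gestational age at scan or adjust for it.
4. Keep UV absolute flow as the declared exposure. Report UV flow per EFW or per HC, and placental thickness relative to EFW, as supplementary analyses.
5. Treat EFW as descriptive in the FGR-control contrast, because EFW or AC percentile helps define the groups.
6. Report the distribution of gestational age at scan by group within each window, so that readers can see whether a gap exists.

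Cost: a little analysis work. Gestational age at scan is already needed to assign scans to the windows, so it should be available from the records. Matching on it may lose a few pairs; adjustment would not.
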